### Secondary outcome measures

3.12

#### Cornell scale for depression in dementia

3.12.1

The CSDD, developed by Alexopoulos et al,^[32]^ is a valid tool for identifying depressive symptoms in patients with cognitive impairment, particularly with AD. Moreover, the validity of the CSDD has been successfully investigated and substantiated, including cross-culturally.^[33–35]^ The CSDD contains 19 questions, each of which can be given a score ranging from 0 (absent) to 2 (severe). The scale is divided into 5 subscales, including mood-related signs, behavioral disturbances, physical signs, cyclic functions, and ideational disturbance.

#### Neuropsychiatric Inventory

3.12.2

The NPI, developed by Cummings et al,^[36,37]^ is the most widely used rating scale for psychiatric and behavior symptoms in neurologically impaired patients. The NPI examines 10 subdomains of behavioral functioning, including delusions, hallucinations, agitation/aggression, dysphoria, anxiety, euphoria, apathy, disinhibition, irritability/lability, and aberrant motor activity. Each factor will be rated for severity (0–3 points) and symptom frequency (0–4 points). The scoring index will include factor scores (frequency × severity) for a total score (0–144 points). Higher scores represent more severe neuropsychiatric symptoms. The NPI has satisfactory validity and reliability in patient settings with high scores for content validity across all items.^[36]^

#### Barthel Index

3.12.3

This scale measures performance in activities of daily living using 10 variables, including fecal incontinence, urinary incontinence, grooming, toilet use, feeding, transfers (e.g., from chair to bed), walking, dressing, climbing stairs, and bathing. Administration of the test usually takes between 5 and 10 minutes. The scale yields a score of 0 to 100 and is interpreted as followings: ≥95 points, completely independent; 75–94 points, mildly dependent; 50–74 points, moderately dependent; 21–49 points, severely dependent; and ≤20 points, completely dependent.^[38]^

## Trial timeline

4

The schedule of outcome measurement assessments is shown in Table 2 (Additional file 3). The trial flowchart is shown in Figure 1 (Additional file 4).

**Table 2 T2:**

Schedule of outcome assessments.

**Figure 1 F1:**
[figure not shown]
Trail protocol flowchart. ADAS-Cog = Alzheimer's Disease Assessment Scale-Cognitive section, BI = Barthel Index, CSDD = Cornell scale for depression in dementia, NPI = Neuropsychiatric Inventory score.

## Monitoring plan

5

An inspector will conduct an audit every 2 weeks. In the early stage of the trial, the inspector will obtain the clinical trial application; prepare trial protocols, clinical evaluation reports, and information consent forms; select qualified researchers; obtain institution ethics committee/institution review board approval; complete personnel training; and identify the protocols. During the trial, the inspector will focus on monitoring the test schedule, ensuring that informed consent is obtained, reviewing the case report forms, verifying the source data, assisting in creating reports regarding adverse events and serious adverse events, filing documents, and evaluating trial implementation. In the later stage of the trial, the inspector will guide the researchers in completing the necessary trial documents according to regulations and explain the responsibilities to the researchers after the trial.

### Statistical considerations

5.1

#### Sample size calculation

5.1.1

We used a power of 1 – β = 0.90, with a significance level of α = 0.05. The difference in ADAS-Cog scores was used as a primary outcome between the 2 groups after treatment. Given μ_α_ = 0.05, μ_β_ = 0.10, standard deviation (σ) = 15, and tolerance error (δ) = 10, we calculated a final effective sample size for n_1_ = n_2_ of approximately 33 per group using the sample size estimation formula.Secondary outcome required sample size: The secondary outcomes were evaluated by CDSS, NPI, and BI, respectively. According to the previous literature data, the required samples were calculated in 32 cases, 28 cases, and 39 cases for each group, respectively.According to the above data, the maximum value of 39 cases for the required sample size. If we assume a patient loss rate of 15%, we will require n_1_ = n_2_ = 45 patients per group. Therefore, we decided that a sample size of 45 patients per group will participate in the trial.

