#### Validity evaluation

5.1.2

A database will be established using EpiData 3.0 software. Statistical analyses will be performed using SPSS 13.0 software (SPSS, Chicago, IL). Continuous data will be expressed as the mean ± standard deviation. The data between groups will be compared using repeated measures analysis of variance. Qualitative data will be compared using the chi-square test. The significance level will be α = 0.05, and 2-sided tests will be used.

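### The stated inputs for ADAS-Cog give 48 to 49 patients per group, not 33, so the stated 90% power does not follow from them at 45 per group

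*Protocol article*

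**What the plan says.** All the inputs are in the protocol article.

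- Section 5.1.1 (Sample size calculation) fixes the error rates: "We used a power of 1 – β = 0.90, with a significance level of α = 0.05".
- It names the comparison: "The difference in ADAS-Cog scores was used as a primary outcome between the 2 groups after treatment". The inputs are "standard deviation (σ) = 15" and "tolerance error (δ) = 10".
- It then reports the result: "we calculated a final effective sample size for n_1_ = n_2_ of approximately 33 per group using the sample size estimation formula".
- It gives 32, 28 and 39 per group for the depression scale, the Neuropsychiatric Inventory and the Barthel Index, and takes 39 as the largest. It continues: "If we assume a patient loss rate of 15%, we will require n_1_ = n_2_ = 45 patients per group".
- Section 5.1.2 (Validity evaluation) names repeated measures analysis of variance for the group comparison and settles the sidedness: "The significance level will be α = 0.05, and 2-sided tests will be used".

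**The concern.** A ratio of standard deviation to difference of 1.5 at 90% power and two-sided 5% normally calls for nearly 50 patients per group, so 33 looks too small at sight. Rounding cannot cover a gap of about 15 per group.

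Two things depend on it. First, the 90% power is the design's stated assurance for its primary outcome, and anyone weighing an inconclusive ADAS-Cog result may refer to it. Second, the final size comes from taking the largest requirement over four outcomes. If the primary figure is too low, that step picks the wrong outcome to size the trial.

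**Working it through.** **Inputs.** Alpha 0.05, power 0.90, SD 15, difference 10, loss 15% (section 5.1.1); two-sided tests (section 5.1.2); 1:1 allocation (section 3.1). Nothing has to be assumed for the sample size itself.

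**Step 1: try to reproduce 33.** For two means, n per group = 2(z_alpha + z_beta)² × SD²/difference². Here SD²/difference² = 225/100 = 2.25.

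| Setting | Calculation | n per group (normal) | n per group (t test) |
|---|---|---|---|
| Two-sided, 90% (as stated) | 2(1.960 + 1.2816)² × 2.25 = 47.3 | 48 | 49 |
| One-sided, 90% | 2(1.645 + 1.2816)² × 2.25 = 38.5 | 39 | 40 |
| Two-sided, 80% | 35.3 | 36 | 37 |
| One-sided, 85% | 32.4 | 33 | 34 |
| Two-sided, 75% | 31.2 | 32 | 33 |

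The stated figure is not reproduced. The two settings that land on or next to 33 both contradict the stated power, and one of them also contradicts the two-sided tests. A one-sample or paired formula halves the first two rows and gives 19.3 (one-sided) or 23.6 (two-sided), so it does not explain 33 either.

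**Step 2: the labels.** The text gives 0.05 and 0.10 as the values of μ_α and μ_β. Those are error rates; the formula needs the normal quantiles 1.960 and 1.2816. Entered literally, they would give 2(0.05 + 0.10)² × 2.25 = 0.10, so they cannot have been what was calculated. This is a slip of notation and does not explain 33.

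**Step 3: does the move from 33 to 45 absorb the error?** The 45 is built on 39: 39 × 1.15 = 44.85, so 45. The protocol's own loss rate leaves 45 × 0.85 = 38.25, about 38 evaluable per group. Two-sided power at SD 15 and difference 10, unadjusted:

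| Evaluable per group | Normal approximation | t test |
|---|---|---|
| 33 | 77.3% | 76.0% |
| 38 (45 less 15%) | 82.8% | 81.8% |
| 39 | 83.7% | 82.8% |
| 45 (no loss) | 88.5% | 87.9% |
| 48 | 90.4% | 89.8% |
| 49 | 91.0% | 90.4% |

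So 90% is not reached at 45 per group, with or without loss. After the planned loss the type II error is about 18% instead of 10%.

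**Step 4: which outcome sets the size?** Corrected, the four requirements are 48 to 49 (ADAS-Cog), 32, 28 and 39. The largest is the primary outcome, not the Barthel Index. Carrying it through the loss allowance gives 48/0.85 = 56.5 (57) or 49/0.85 = 57.6 (58) randomised per group.

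**Step 5: the loss allowance.** Dividing is the usual form: 39/0.85 = 45.9, so 46. The difference is one patient per group.

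**The case against.** The strongest reply is that the trial will not be analysed by an unadjusted comparison at one time point. Section 5.1.2 plans repeated measures analysis of variance, and there are four assessments including baseline, so within-patient correlation may reduce the variance. This is partly right. With adjustment for baseline, the requirement becomes 47.28 × (1 − ρ²). That is 33.0 at ρ = 0.55, and it equals 38 when ρ² = 1 − 38/47.28 = 0.196, so ρ is about 0.44. The actual power of the planned analysis is therefore unknown. But section 5.1.1 states no correlation and credits no variance reduction, so this cannot make 33 follow from its inputs or support the 90%. A correlation chosen now to fit 45 per group would be a justification made to match the size.

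A second reply is that 39 evaluable would be enough for a one-sided test at 90% power (38.5, rounded up). That is true arithmetically, but section 5.1.2 specifies two-sided tests.

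Three stronger readings are tempting, and the documents do not support them:

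- **That 45 per group has 82% power without qualification.** The 82% belongs to about 38 evaluable; if all 45 were analysed it would be about 88%.
- **That 33 shows a one-sided 85% calculation was used.** Two-sided 75% power gives 32 to 33 as well, and so would a baseline correlation of about 0.55. How 33 arose cannot be told.
- **That the trial has been shown to lack 90% power.** What is shown is that 90% does not follow from the stated inputs for the stated comparison.

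**Conclusion.** The point holds in that form. From its own inputs, section 5.1.1 should report 48 per group (49 with the t distribution) instead of 33, an understatement of about 15 per group. The primary requirement exceeds the 39 on which the trial size was built, so the later steps do not repair it.

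The power figures of about 82% after loss and 88% without rest on SD 15, a true difference of 10, two-sided 5% testing and an unadjusted post-treatment comparison of two equal groups. The shortfall is moderate, but it concerns the primary outcome and is certain as arithmetic. An analysis plan that is not shown could not change it, because inputs and result are printed together and disagree. The notation and the 45-versus-46 question are minor, and the conclusion does not depend on them.

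**What to change.** In section 5.1.1:

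1. Replace 33 by 48 evaluable per group (49 with the t distribution) for ADAS-Cog, and state there that the test is two-sided.
2. Drop the claim that 39 is the largest requirement across outcomes.
3. Keep 90 patients and restate the power: about 82% after the assumed 15% loss (about 38 evaluable per group), about 88% with no loss, for the unadjusted post-treatment comparison.
4. Claim a higher power for a baseline-adjusted or repeated measures analysis only if a within-patient correlation is stated and justified.
5. As clean-up, give the quantiles 1.960 and 1.2816 in place of 0.05 and 0.10, and note that 39/0.85 rounds up to 46.

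The cost is wording and a less favourable power statement. No extra patients are needed and conduct does not change. Section 8.1 says recruitment is ongoing, so as of the article the correction could be made before results are known.

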### Study design

3.1

This randomized parallel-design controlled trial will be conducted in the Beijing Geriatric Hospital of China. A total of 90 patients with AD will be recruited and randomized into 2 groups: intervention and control group (n = 45 per group). Random number sequences will be generated by a statistician using SAS software, and sealed envelopes will be used for randomization. The statistician who randomly assigned the participants will not be responsible for the enrollment of subjects, and another independent statistician will be responsible for uncovering at the end of the trial. In the intervention group, along with conventional drug therapy, the patients will be subjected to reminiscence therapy for 35 to 45 minutes each time, and 2 times/wk for 12 consecutive weeks. The patients in the control group will undergo conventional drug therapy. The primary outcome will be changes in Alzheimer Disease Assessment Scale-Cognitive section (ADAS-Cog) scores in patients from each group, and the secondary outcomes are the changes of Cornell scale for depression in dementia (CSDD), Neuropsychiatric Inventory score (NPI), and Barthel Index (BI) scores. Evaluation will be performed before treatment, at 4 and 12 weeks of treatment, and 12 weeks after treatment.

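### Section 5.1.1 appears to apply the 15% loss allowance by multiplying rather than dividing, so 45 per group leaves about 38 evaluable patients, one short of the plan's own 39 (minor)

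*Protocol article*

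**What the plan says.** The protocol article, section 5.1.1 (Sample size calculation), gives a requirement of about 33 per group for the primary outcome, ADAS-Cog. For the three secondary scales (Cornell depression scale, NPI, Barthel Index) it gives 32, 28 and 39. It adopts the largest, "the maximum value of 39 cases for the required sample size", which is the Barthel Index figure.

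The next sentence makes the allowance for loss: "If we assume a patient loss rate of 15%, we will require" 45 in each group. The section closes with "we decided that a sample size of 45 patients per group will participate in the trial".

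Section 3.1 (Study design) carries the number forward: "A total of 90 patients with AD will be recruited and randomized into 2 groups". The abstract also gives 45 per group.

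**The concern.** The three figures in this step (39 needed, 15% lost, 45 enrolled) are all stated, and they do not fit together. If 15% of 45 patients are lost, fewer than 39 remain. The stated size therefore does not deliver the number from which it is derived, and the real margin for loss is a little smaller than the 15% the text claims.

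What is at stake is the accuracy of a stated figure and the formula behind it. The formula matters beyond this one number, because the same step will be reused if the base figure is revised.

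**Working it through.** **Inputs.** Required evaluable patients per group 39, loss rate 15%, planned 45 per group, all from section 5.1.1. Power 0.90 and alpha 0.05 are from section 5.1.1, and two-sided testing is from section 5.1.2.

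**Step 1: reproduce the plan's figure.** Multiplication gives 39 x (1 + 0.15) = 44.85, which rounds up to 45. This matches exactly. The article does not show its formula, so multiplication is an inference. Truncating 45.88 (step 2) would also give 45.

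**Step 2: the figure that meets the stated aim.** If a share d of n enrolled patients is lost, n x (1 - d) remain, so n = required/(1 - d).
- 39/(1 - 0.15) = 39/0.85 = 45.88, rounded up to 46.

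**Step 3: what each size leaves at 15% loss.**
- 45 x 0.85 = 38.25, about 38 patients, against 39 required.
- 46 x 0.85 = 39.1.

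**Step 4: the loss that 45 can bear.** 45 - 39 = 6, and 6/45 = 13.3%.

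**Step 5: the cost in power.** The article gives no difference or SD for the Barthel Index, so this needs an assumption about what 39 delivers. By normal approximation, the standardised difference d solves 39 = 2 x (1.960 + z)²/d², where z is the normal quantile for the assumed power. Power at 38 is then Φ(d x √(38/2) - 1.960).

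| Power assumed at 39 | Implied d | Power at 38 |
|---|---|---|
| 90% | 0.734 | 89.2% |
| 80% | 0.634 | 79.0% |

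The loss is about 1 point or less in either case.

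**Step 6: the primary outcome as stated.** The stated need is about 33. At 15% loss, 45 leaves about 38, which exceeds it. Against 33, a group of 45 can lose 12 patients (12/45 = 26.7%).

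**Step 7: the base figure, which is a separate matter.** With SD 15, difference 10, two-sided 0.05 and 90% power, n = 2 x (15 x (1.960 + 1.282)/10)² = 47.3, or 48 per group, not 33. From 48, division gives 48/0.85 = 56.5, or 57. Multiplication gives 48 x 1.15 = 55.2, or 56, and 56 x 0.85 = 47.6, again just short. The loss-step error therefore persists with a corrected base.

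**The case against.** The best case on the other side accepts the division and disputes that it matters.

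- **Size.** The gap is one patient per group and under about one power point. The 15% is itself a round assumption with no source given. This stands, and it is why the point is minor.
- **Scope.** Only one secondary scale falls short. The stated needs for the primary outcome and the other two scales (33, 32, 28) are all met by 38. This also stands.
- **Rounding of the 39.** If 39 was rounded up from 38.25 or less, correct division would also return 45 (38.25/0.85 = 45.0). The article shows no unrounded value, so this cannot be excluded. But the text starts the loss step from 39, and from 39 the step fails.
- **A larger fault in the same section.** The primary figure of 33 does not follow from its inputs, and correcting it would supersede both 45 and 46. That is true, but step 7 shows the loss formula still has to be put right.

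A reader might go further and infer that the trial must enrol 46 per group (92 in all), or that it is underpowered because of this step. The documents do not support that: the shortfall is one patient on a secondary outcome, and 46 would leave about 39, still well below the 48 that the stated primary inputs require. A reader might also cite the chance of actually keeping 39. With an independent 15% loss risk it is 0.48 in one arm and 0.23 in both with 45 enrolled. With 46 it is only 0.62 and 0.38, so both arms would still miss the target together 62% of the time. A loss allowance adjusts the expected number, and these probabilities do not show a material defect.

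**Conclusion.** Wrong as written, and minor. From the plan's own 39 and 15%, the enrolled number is 46 per group. The stated 45 leaves about 38 evaluable patients and bears 13.3% loss rather than 15%. This part rests only on stated figures and on reading the loss rate as a share of those enrolled.

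The power cost, 90% to about 89.2% for the Barthel Index, is conditional on 39 giving 90% power, because that outcome's inputs are not given.

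The mismatch between 33 and about 48 for the primary outcome is the larger problem in section 5.1.1. Correcting the loss step does not resolve it.

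**What to change.** Keep 45 per group and restate in section 5.1.1 what it delivers, for example: *45 patients per group leave about 38 evaluable patients at 15% loss; 39 are retained if loss is at most 13.3% (6 of 45).* State the loss step as division by (1 - loss rate), and use it for whatever base figure finally stands.

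The cost is one sentence, with a stated figure slightly less favourable than the present one. No extra patients are needed for this correction, and the 45 and 90 in the abstract and section 3.1 can stay as far as this point goes. The base figure of 33 needs its own correction.

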#### Validity evaluation

5.1.2

A database will be established using EpiData 3.0 software. Statistical analyses will be performed using SPSS 13.0 software (SPSS, Chicago, IL). Continuous data will be expressed as the mean ± standard deviation. The data between groups will be compared using repeated measures analysis of variance. Qualitative data will be compared using the chi-square test. The significance level will be α = 0.05, and 2-sided tests will be used.

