### Primary outcome measure

3.11

The primary outcome is defined as the difference in ADAS-Cog scores before treatment, at 4 and 12 weeks of treatment, and 12 weeks after treatment. The ADAS-Cog, developed by Rosen et al,^[26]^ is a scale to assess cognitive function of patients with mild to moderate AD, and examines multiple cognitive domains including memory, language, praxis, and orientation. The ADAS-Cog has been well applied in trials of symptomatic treatments for mild-to-moderate AD, and its reliability and detection effectiveness have been confirmed to be acceptable by many clinical studies.^[27–29]^ Overall, it is widely used as an outcome measure in clinical trials that evaluate the cognitive changes of AD.^[30,31]^

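### Repeated measures ANOVA over four visits, pre-treatment included, does not target the post-treatment ADAS-Cog difference used for sizing and, in its classical form, drops incomplete patients; a baseline-adjusted mixed model would serve better

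*Protocol article*

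**What the plan says.** Section 5.1.2 (Validity evaluation) gives one method for the group comparison: "The data between groups will be compared using repeated measures analysis of variance". The tests are two-sided: "The significance level will be α = 0.05, and 2-sided tests will be used". The section does not say which visits enter as levels, which term decides the trial, whether baseline is a covariate, or how missing visits are treated.

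The visits are set out in section 3.1: "Evaluation will be performed before treatment, at 4 and 12 weeks of treatment, and 12 weeks after treatment". Section 3.11 builds the primary outcome from all four: "The primary outcome is defined as the difference in ADAS-Cog scores before treatment, at 4 and 12 weeks of treatment, and 12 weeks after treatment". Section 3.1 words it as change: "The primary outcome will be changes in Alzheimer Disease Assessment Scale-Cognitive section (ADAS-Cog) scores in patients from each group".

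Section 5.1.1 sizes the trial on something narrower: "The difference in ADAS-Cog scores was used as a primary outcome between the 2 groups after treatment", with a difference of 10, SD 15 and 90% power. It expects 15% loss and enrols 45 per group. Section 3.5 withdraws patients whose complications or new illness could affect the outcome, and those who take up other therapies.

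**The concern.** A repeated measures ANOVA with two groups and four visits offers two tests of treatment, and neither estimates the difference on which the trial was sized.

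- The group main effect compares the patients' averages over all visits. If the pre-treatment visit is one of them, a visit with an expected difference of zero is averaged in, and the effect shrinks.
- The group-by-time term is not diluted. It asks on 3 degrees of freedom whether the profiles differ in any way, and returns no single difference with a confidence interval. Its usual F test also relies on sphericity, over visits at about weeks 0, 4, 12 and 24.

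Classical repeated measures ANOVA also needs a score at every visit. A patient seen at weeks 4 and 12 but lost afterwards contributes nothing. Under the withdrawal rules in section 3.5, those lost may differ in outcome from those who stay, so an analysis of completers could be biased.

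At stake are the power of the primary comparison and whether its result can be read as the planned difference.

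**Working it through.** **Inputs from the protocol (section 5.1.1):** SD σ = 15, difference 10, power 90%, α = 0.05 (two-sided by section 5.1.2), largest required size 39 per group, 15% loss, 45 enrolled per group. I use n = 39 complete patients per arm; 45 × 0.85 = 38.25, and 38 leads to the same conclusions.

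**Assumed, not in the protocol:** compound symmetry, correlation ρ between visits of 0.5 to 0.8, no clustering by therapy group, and the patterns of true differences below.

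**The plan's own figure.** Section 5.1.1 gives about 33 per group. Its inputs give 2(1.960 + 1.282)² × 15²/10² = 47.3, so 48 per group two-sided (39 one-sided). The 33 is not reproduced. That is a separate matter, but it sets the benchmark: an unadjusted t-test at one post-treatment visit with 39 per arm has SE 15√(2/39) = 3.40 and power of about 84%. Part of any shortfall from 90% is therefore due to sample size.

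**Group main effect, baseline as a level.**
- Expected estimate for differences 0, 10, 10, 10: 30/4 = 7.5.
- Variance of a patient's four-visit mean: σ²(1 + 3ρ)/4. At ρ = 0.6 this is 225 × 2.8/4 = 157.5, so the SE of the arm difference is √(2 × 157.5/39) = 2.84.
- Noncentral t on 76 df: power 74%.

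**Group-by-time.**
- Noncentrality λ = (n/2) Σ(dⱼ − d̄)² / [σ²(1 − ρ)].
- For 0, 10, 10, 10: Σ = 7.5² + 3 × 2.5² = 75. At ρ = 0.6, λ = 19.5 × 75/90 = 16.25. Noncentral F on 3 and 228 df: power 93%.
- For 0, 5, 10, 5: Σ = 50, λ = 10.83, power 79%.

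**Baseline-adjusted week 12.** Residual SD 15√(1 − ρ²) = 12 at ρ = 0.6; SE = 12√(2/39) = 2.72; power 95% for a 10-point difference.

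**Power over the range of ρ (39 per arm):**

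| True differences (weeks 0, 4, 12, 24) | Test | ρ = 0.5 | 0.6 | 0.7 | 0.8 |
|---|---|---|---|---|---|
| 0, 10, 10, 10 | Main effect (estimates 7.5) | 79% | 74% | 70% | 66% |
| | Group-by-time | 86% | 93% | 98% | >99% |
| | Adjusted week 12 | 92% | 95% | 98% | >99% |
| 0, 5, 10, 5 | Main effect (estimates 5) | 45% | 41% | 38% | 35% |
| | Group-by-time | 68% | 79% | 90% | 98% |
| | Adjusted week 12 | 92% | 95% | 98% | >99% |
| 0, 5, 5, 10 | Main effect (estimates 5) | 45% | 41% | 38% | 35% |
| | Group-by-time | 68% | 79% | 90% | 98% |
| | Adjusted week 12 | 39% | 44% | 53% | 68% |

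**Loss of patients.** 0.15 × 90 = 13.5, so up to about 14 patients would be left out with whatever scores they had. The table uses 39 per arm for every method, so it shows no gain from keeping partial follow-up.

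**The case against.** A reader might infer that the protocol makes the pre-treatment score an outcome level, takes the group main effect as the deciding test and keeps only completers. It states none of these. Baseline as a level is the natural reading of sections 3.1 and 3.11; completers-only follows from the classical method; the main effect is one of two candidates. Section 3.1's wording in terms of change fits group-by-time at least as well, and that term is not diluted. With a constant effect and ρ = 0.6 it has 93% power against 95% for the adjusted week-12 comparison. This objection stands, and the dilution must be stated conditionally.

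A reader might also take 41% against 95% as the cost of the planned method. That contrast depends on an effect that peaks at the visit chosen for the comparison. With the last two differences changed so that the peak falls at follow-up (0, 5, 5, 10), adjusted week 12 has 44% and group-by-time 79%. The protocol does not name week 12 as the primary time point.

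The covariate, sphericity correction and missing-data rule are commonly left to an analysis plan, which is not shown. Their absence is no fault in itself. The point rests on the method the article does name. The enrolment margin for 15% loss also largely covers the loss of numbers, and epsilon corrections for sphericity exist.

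Finally, bias from dropout is plausible given section 3.5, but no dropout pattern is documented and its size cannot be computed.

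**Conclusion.** The point holds in a conditional form, as something that should be fixed.

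- **If the group main effect is tested with baseline as a level,** a constant 10-point effect is estimated as 7.5. Power is about 66–79%, below the planned 90% and below the 84% of a plain post-treatment t-test at the same size.
- **If group-by-time is tested,** power is 86% to over 99% for the constant effect and 68–98% for 0, 5, 10, 5. The test still gives no estimate of the post-treatment difference in section 5.1.1.
- **In either case,** the classical method excludes up to about 14 of 90 patients at the expected loss.

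These figures rest on SD 15, 39 per arm, compound symmetry and ρ of 0.5–0.8; the last two are assumptions. A reader might infer that the trial could produce a false positive through this choice. It could not through dilution: with no treatment effect, both terms have an expected difference of zero under randomisation. The cost is in efficiency, interpretability and exposure to selective dropout.

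**What to change.** Replace the sentence on the group comparison in section 5.1.2 with wording such as:

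> Post-baseline ADAS-Cog scores (weeks 4, 12 and 24) will be analysed with a linear mixed model for repeated measures, using all available post-baseline scores of randomised patients. Fixed effects are baseline ADAS-Cog, arm, visit, arm-by-visit and baseline-by-visit; the covariance is unstructured. The primary result is the adjusted arm difference at [named time point] with its 95% confidence interval.

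Use the same model for CSDD, NPI and BI, each with its own baseline score.

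The time point is a decision about the primary question. Week 12, the end of treatment, fits section 5.1.1, but the sponsor must confirm it before the database is locked. Sections 3.1 and 3.11 should then name the same contrast.

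The cost is small: no new visits or data, a change of wording, and a check that the named SPSS version can fit the model. There are two minor downsides. The model assumes that data are missing at random. It also omits patients with no post-baseline score unless baseline is modelled jointly with the later visits.
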